## Abstract

Supplemental Digital Content is available in the text

## Introduction

1

Degenerative knee osteoarthritis (KOA) is a disease accompanied by degeneration and wear of the knee joint cartilage and osteochondral defect.^[1]^ Clinical symptoms are knee pain, fatigue, limited range of motion, swelling and tenderness around the joints, friction noises during exercise, and formation of osteophytes.^[2]^ The risk factors for degenerative KOA include gender, increased age, and obesity, and the incidence in women is known to be about three times higher than that in men.^[3]^ Although the prevalence of degenerative KOA slightly differs in studies depending on gender, age, and region, it has been reported to be about 20% to 30% for women and 8% to 15% for men in the middle-aged and elderly population aged over 50 years.^[4]^ The morbidity rate for degenerative KOA has increased with improvements in living conditions and extended lifespans, and the age of onset is also getting younger. This not only significantly affects the life of the elderly population but also increases medical service expenses and socioeconomic costs. Therefore, there is an increasing need for medical knowledge and healthcare services for the middle-aged and elderly patients who suffer from degenerative KOA.^[5,6]^

The treatment methods for degenerative KOA are largely based on nondrug therapy, drug therapy, and surgical treatment. Nondrug therapy involves weight loss, stretching, and muscle-strengthening exercises. If there is no response to nondrug therapy, drug therapy is considered. Drug therapy is classified as topical treatments such as intra-articular steroid injections, hyaluronic acid injections, and capsaicin-based external agents and oral therapies such as nonsteroidal anti-inflammatory drugs, acetaminophen, glucosamine, chondroitin, tramadol, and narcotic analgesics.^[7]^ If pain cannot be resolved with these methods, surgical treatment is considered. Surgical treatments include arthroscopic surgery, autologous chondrocyte implantation, autologous osteochondral transplantation, osteotomy, and arthroplasty. Osteotomy or artificial joint replacement is usually performed in cases of severe joint destruction and deformation, whereas arthroscopic surgery, autologous chondrocyte implantation, and autologous osteochondral transplantation are commonly performed in patients with chronic pain with relatively limited joint destruction.^[8]^

In arthroscopic surgery, an endoscope and the surgical instrument are inserted into the joint through a small incision of less than 1 cm to conduct a diagnostic arthroscopic examination and perform joint irrigation, debridement, or microfracture depending on the patient's condition.^[8]^ The advantages of this procedure include the relatively few complications, short rehabilitation period, and no interference with other subsequent surgeries. But, recent research has shown that the benefits of arthroscopic surgery are lost 1 to 2 years after surgery and that the surgery is not effective in treating osteoarthritis except in cases with acute trauma or symptomatic meniscal injury.^[9,10]^ In autologous chondrocyte implantation, regeneration of cartilage tissue is induced by culturing the collected autologous chondrocytes in vitro for about 3 to 6 weeks and then transplanting them into defective joint cartilage sites.^[8]^ This technique can be applied to areas with relatively large cartilage losses and it causes less damage at the donor site since a very small amount of cartilage tissue is collected. Some research shows therapeutic effects such as pain relief and functional enhancement in over 70% to 90% of cases if the procedure is performed on appropriately selected patients.^[8]^ However, a 15-year long-term follow-up study on patients who received autologous chondrocyte implantation showed 59% failure rate, with limited improvement reported in some of the young patients.^[11]^ Finally, autologous osteochondral transplantation is used for small cartilage defects of about 2 cm^2^ or less. The collected bone cartilages are transplanted into a cartilage defect site.^[8]^ It allows early weight-loading, is inexpensive, and can be performed in a single operation. The progress of this surgery is similar to that of autologous chondrocyte implantation.^[12]^ However, according to a study that followed up patients aged over 40 years for at least 2 years after autologous osteochondral transplantation, 40% of the patients underwent additional artificial joint replacement or another osteochondral transplantation.^[13]^ Thus, there is a need for the safe and effective complementary treatment for patients who have experienced residual pain and discomfort after surgeries but have not deteriorated to the state of absolute knee instability requiring artificial joint replacement or osteotomy.

Thread-embedding acupuncture (TEA) and electroacupuncture (EA) treatments are applied as complementary and alternative therapies for musculoskeletal pain disorders. In TEA, a thread is embedded inside the needle into the acupoint, which can produce a sustained stimulation effect of the embedded thread in addition to stimulation effect of the conventional acupuncture.^[1]^ TEA is used for neck pain,^[14]^ low back pain,^[15]^ shoulder pain,^[16]^ and for sequelae of facial paralysis.^[17]^ A systematic literature review on TEA for degenerative KOA^[18]^ included 3 randomized controlled trials published in China, and all 3 studies showed significant therapeutic effects in the intervention group that received TEA. EA involves the application of electrical stimulation along with acupuncture stimulation, and is widely used in clinical practice to relieve acute or chronic pain.^[1]^ It has been used in the treatment of neck pain,^[19]^ low back pain,^[20]^ and neuropathic pain,^[21]^ and is a method frequently used in the treatment of degenerative KOA. In Korea, EA is recommended as one of the most common treatments for knee pain in clinical practice.^[22]^

Despite the fact that TEA and EA are being used in patients with degenerative KOA in the current clinical setting, there is insufficient clinical evidence to support their use. Furthermore, there have been no reports of clinical trials providing the evidence for a combination of TEA and EA in patients with degenerative KOA who complain of pain and dysfunction even after a certain period of recovery after arthroscopic surgery, autologous chondrocyte implantation, or autologous osteochondral transplantation. Therefore, our researchers planned a preliminary clinical trial for evaluating the efficacy and safety of TEA and EA combination treatment in patients with degenerative KOA who complain of pain even after arthroscopic surgery, autologous chondrocyte implantation, or autologous osteochondral transplantation.

## Methods

2

### Objective

2.1

This clinical trial has 2 objectives. First, it aims to evaluate the clinical efficacy of TEA and EA combination treatment by comparing changes in visual analogue scale (VAS) at week 4 between the (TEA + EA + Usual care) group and the (Usual care only) group. Second, it will assess the safety of the TEA and EA combination treatment by examining the adverse events (AEs) after the procedure.

### Study design

2.2

This study is designed as a 2-group, parallel, single-center, randomized, controlled, assessor-blinded trial. Figure 1 shows the flowchart of this trial. A total of 36 patients will be recruited based on the inclusion/exclusion criteria (Table 1) from subjects who will visit the Daejeon University Daejeon Korean Medicine Hospital between April and December 2020. Subjects will be recruited through the online hospital website and bulletin board, regional newspapers, and advertisement panels on public transportation.

**Figure 1 F1:**
[figure not shown]
Study flow with outcome assessments.

**Table 1 T1:**
[figure not shown]
Inclusion and exclusion criteria.

Subjects voluntarily consent to participating in the clinical trial and sign the written consent form. A series of surveys and tests will be performed to determine eligibility, which include a demographic information survey, interview on medical history, questionnaire assessments, blood tests, electrocardiogram examinations, knee radiographic examinations, and urine human chorionic gonadotropin tests for women of childbearing potential. Once eligibility has been determined, the subjects will be notified of their availability to participate, and eligible subjects will be randomized to the (TEA + EA + Usual care) group and (Usual care only) group in a 1:1 ratio. The (TEA + EA + Usual care) group will receive TEA treatment once a week for 4 weeks for a total of 4 sessions and EA twice a week for a total of 8 sessions while continuing usual care. The (Usual care only) group will only receive usual care for 4 weeks. During the 8-week study period, there will be 3 visit assessments (weeks 2, 4, and 8) and 1 nonvisit assessment (week 6).

### Sample size

2.3

This is a preliminary pilot study designed to assess the feasibility of the study and collect information on the sample size calculation for the entire study. Therefore, the sample size has been assumed to be 14 per group and 28 in total, considering the minimum range that allows efficacy assessment and the number of subjects that can be recruited during the planned study period, rather than being based on statistical calculations. Considering the dropout rate of 20%, the actual recruitment number has been determined to be 18 per group and 36 in total.

### Randomization and blinding

2.4

Randomization should be performed to ensure that treatment assignment is not biased and it is not exposed to the subjects as well as the investigators. A statistician unrelated to conducting and assessment of the clinical trial will randomly assign 18 subjects to each group using the statistical program SAS Version 9.4 (SAS institute. Inc, Cary, NC) with the same probability for each individual. The independent statistician will keep the randomization table to make sure that it is not disclosed.

Since the participants will be divided into the (TEA + EA + Usual care) group and (Usual care only) group, blinding of the practitioners and subjects will be difficult due to the significant differences in the procedures performed in each group. However, the assessors will be blinded to control the bias as much as possible. Efficacy assessments for subjects will be conducted by investigators who have not performed the intervention and the randomization. The Assessors simply ask questions on evaluation items and case report forms (CRFs), and they are blinded to the treatment the subjects are receiving.

### Interventions

2.5

#### Thread-embedding acupuncture combined with electroacupuncture

2.5.1

Table 2^[1,18,23–26]^ and Table 3^[1,22,27,28]^ summarize of the details of TEA and EA treatments. The subjects in the (TEA + EA + Usual care) group will receive the combined treatment consisting of TEA once a week and EA twice a week for 4 weeks while continuing usual care. TEA and EA treatments will be performed by a licensed Korean Medicine doctor with at least 3 years of clinical experience in TEA. The procedure site will be thoroughly disinfected using 78% alcohol cotton before and after the procedure to prevent infection.

**Table 2 T2:**
[figure not shown]
TEA treatment details based on standards for reporting interventions in clinical trials of acupuncture (STRICTA) checklist.

**Table 3 T3:**
[figure not shown]
EA treatment details based on standards for reporting interventions in clinical trials of acupuncture (STRICTA) checklist.

For TEA, a 29-gauge 30-mm needle or a 29-gauge 60-mm needle with polydioxanone threads manufactured by Dongbang Medical Co will be used. The appropriate length will be determined based on the depth and direction of the insertion at each acupoint and the subject's physique and muscle conditions. The needles will be inserted after properly exposing the procedure site by having the patient bend the knee at 45° in a sitting position. The practitioner will select 8 to 10 acupoints from the acupoint pool of EX-LE4, ST35 = EX-LE5, EX-LE2, ST34, SP10, ST36, GB34, SP9, LR8, and BL40 based on the region of pain, meridian diagnosis, motion, and palpation with controlled finger pressure.

For EA, gamma-sterilized disposable needles (0.25 × 40 mm, Dongbang Medical Co, Korea) will be used. After the subject is placed in the lateral position and the procedure site is properly exposed, acupuncture will be performed. The needles will be inserted into approximately 10 acupoints from the acupoint pool of EX-LE4, ST35 = EX-LE5, ST34, SP10, BL40, LR9, ST31, ST32, GB29, GB30, BL24, BL25, and BL26, including the fixed 6 acupoints ST34, SP10, BL40, LR9, BL24, and BL25. Electrical stimulation will be given at 2 Hz for 20 minutes on (ST34-SP10), (BL40-LR9), and (BL24-BL25).

#### Usual care

2.5.2

The participants in the (Usual care only) group will receive conventional usual care alone for 4 weeks. Usual care in this study is defined as routine medical care by standard conventional treatment. The participants will receive usual care such as drug therapy, physical therapy, manipulation, and exercise therapy for knee pain relief depending on their individual needs. After the end of the clinical trial, up to 2 sessions of TEA compensatory treatment will be provided for the subjects of the (Usual care only) group who wish to receive it.

#### Cointerventions

2.5.3

All subjects will be allowed to receive usual care for knee pain relief and instructed to report the details and the frequency of usual care received during the study period to the investigators in charge. However, other Korean medical treatments for knee pain relief such as acupuncture (eg, acupuncture, EA, pharmacopuncture, TEA), moxibustion, herbal medicine, cupping, etc are not permitted, and invasive treatments (injections and surgical treatment) on the knee are also prohibited. The investigators will record significant drug/nondrug therapy in the CRF.

In this study, acetaminophen with a maximum dose of 3000 mg (6 T/day) or less per day will be provided as the rescue drug, and subjects will be instructed to take and report it only when the pain is severe and unbearable during the clinical study period. Assessments will be performed without taking the rescue drug on the day of assessment for weeks 2, 4, 6, and 8, and the rescue drug can be taken if necessary after the assessment has been completed.

Other concomitant medications (including treatment drugs for other diseases or AEs) that are believed to not have a significant impact on the interpretation of the results of this clinical trial will be allowed at the investigator's discretion. If a drug is taken arbitrarily by the subject without prior notice or the decision of the investigator and this drug is believed to have significant effect on the assessments of this clinical trial, the subject will be dropped out.

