### Statistical analysis

2.8

Analysis is carried out using the program SAS Version 9.4 (SAS institute. Inc, Cary, NC). All statistical analyses are two-tailed test, and the significance level will be set to 5%. For missing values, multiple imputation is used.

The full analysis set and the per-protocol set will be used in the analysis of data obtained from the subjects. The full analysis set refers to minimizing subjects excluded from analysis and analyzing the set of subjects excluded only for justifiable reasons. The per-protocol set refers to the analysis of the subject group with no protocol violations who have completed at least 75% of the participation level (at least 3 TEA and at least 6 EA in the intervention group) and all measurements for endpoints indicated in the protocol.

Descriptive statistics are presented for the demographic characteristics and basic clinical data such as gender, age, medical history, and medication history by intervention group. For continuous variables, comparison by each group will be analyzed by an independent *t* test or Wilcoxon rank sum test after presenting the means and standard deviations, along with the 95% confidence intervals, if necessary. For categorical variables, analysis will be carried out using the Chi-squared test or Fisher Exact test after presenting the frequency and percentiles.

The primary efficacy endpoint is the mean change in VAS at week 4 compared to baseline, and will be analyzed using an analysis of covariance with each group as the fixed factor and the VAS before intervention and age as the covariates. If there is a clinical difference between groups in demographic and preintervention characteristics, it will be corrected by adding it as a covariate if needed. The analysis for secondary endpoints will be carried out using the same method as for the primary efficacy endpoints. In addition, to analyze the differences in measurements before and after the intervention within each group, a paired *t* test or Wilcoxon signed-rank test will be used for the primary and secondary efficacy endpoints. To test for the difference in trends by visit, repeated-measures analysis of variance will be performed. For multiple comparison correction, Dunnett procedure will be used.

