### Withdrawal and dropout

2.9

The study completion of all subjects participating in the clinical trial will be recorded by the investigators. Reasons will be recorded in case the procedure is discontinued or if a subject is dropped out. The study will be discontinued for subjects in case a violation of the inclusion/exclusion criteria is discovered during the study, in case of protocol violations, or in case continuation of the clinical trial is difficult due to the occurrence of an AE or a SAE.

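### Subjects dropped for self-medication, protocol violations or late-found ineligibility have no stated further assessment, so their week-4 VAS can be lost for reasons related to pain and arm

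*Protocol article*

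**What the plan says.** Two conduct rules in the protocol article take randomised subjects out.

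- **Section 2.5.3 (Cointerventions).** The rule covers a drug taken on the subject's own initiative, without notice to or a decision by the investigator. If "this drug is believed to have significant effect on the assessments of this clinical trial, the subject will be dropped out".
- **Section 2.9 (Withdrawal and dropout).** "The study will be discontinued for subjects in case a violation of the inclusion/exclusion criteria is discovered during the study", and also "in case of protocol violations, or in case continuation of the clinical trial is difficult due to the occurrence of an AE or a SAE". Protocol violations are not graded by seriousness.

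Both rules end the subject's participation in the study, not only the treatment. No section says that such a subject is still assessed at the remaining time points.

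On analysis, section 2.8 states: "For missing values, multiple imputation is used". It names a full analysis set, which is meant to keep exclusions to a minimum, and a per-protocol set restricted to subjects without violations. The primary endpoint (section 2.6) is the change at week 4 in a 100-mm VAS marked by the patient. Subjects and practitioners are not blinded; assessors are (section 2.4).

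**The concern.** A subject removed before week 4 contributes no week-4 VAS. That would do little harm if removal had nothing to do with the outcome, but two of the triggers plausibly do.

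- Taking an off-plan analgesic, or seeking one of the knee treatments that section 2.5.3 prohibits, is a natural response to poorly controlled pain, and pain is the primary outcome.
- Section 2.6 itself expects effective pain control in the intervention group to lower the rescue dose needed. On that reasoning, analgesic use is related to arm as well as to pain.

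If more high-pain subjects are lost from usual care, a real benefit is partly hidden. If more are lost from the TEA + EA arm, the benefit is exaggerated. The trial is a pilot, but efficacy on the week-4 VAS is its first objective (section 2.1), and its data are meant to inform the sample size of the full study (section 2.3). Outcomes that were never collected cannot be restored by a later analysis plan.

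**Working it through.** **The plan's own figure.** Section 2.3 assumes 14 evaluable subjects per group and 20% dropout: 14 / (1 − 0.20) = 17.5, rounded up to 18 per group and 36 in total. This reproduces. The plan therefore tolerates 18 − 14 = 4 losses per arm, whatever their reason.

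**Inputs the protocol does not give (assumptions).** SD of VAS change 20 mm. Normal outcome. Removal only from the worse half of each arm, with probability 2p there and 0 elsewhere, so a fraction p of the arm is lost. Correlation ρ = 0.6 between the week-2 value and the outcome.

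**Completers.** In SD units, the mean of those retained shifts by m(p) = −2p × 0.3989 / (1 − p), where 0.3989 is the standard normal density at zero.

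- p = 0.20: −0.1596 / 0.80 = −0.1995, or −3.99 mm
- p = 0.15: −0.1197 / 0.85 = −0.1408, or −2.82 mm
- p = 0.05: −0.0399 / 0.95 = −0.0420, or −0.84 mm
- p = 2/18: −0.0997, or −1.99 mm
- p = 1/18: −0.0469, or −0.94 mm

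**After regression imputation on week 2.** The variance among those retained is v = 1 − m². The slope is β = ρv / (ρ²v + 1 − ρ²). The remaining shift is m(1 − βρ). For p = 0.20, v = 0.960 and β = 0.584, so the shift is −0.1995 × 0.649 = −0.1295, or −2.59 mm. For p = 0.05 it is −0.54 mm.

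**Bias in the difference (TEA + EA minus usual care).**

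| Removed, usual care vs TEA + EA | Completers | Imputed, ρ = 0.6 | Imputed, ρ = 0.8 |
|---|---|---|---|
| 20% vs 5% | 3.15 mm | 2.05 mm | 1.17 mm |
| 15% vs 5% | 1.98 mm | 1.28 mm | 0.72 mm |
| 2/18 vs 1/18 | 1.06 mm | 0.68 mm | 0.38 mm |
| equal | 0 | 0 | 0 |

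Swapping the arms reverses the sign.

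**Check at the trial's size.** A separate simulation used ANCOVA on baseline with no imputation, 18 per arm, true effect zero and 4,000 runs per setting. It assumed SD 15 to 25 mm, a baseline to week-4 correlation of 0.5, and removal correlated 0.5 to 1.0 with week-4 pain.

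- 4 removed from one arm only: shift about 2.1 to 7.0 mm, type I error about 7% to 17%
- 4 versus 1 removed: shift about 1.5 to 5.1 mm
- 4 versus 4 removed: shift about 0
- everyone followed and analysed: shift about 0, type I error about 5%

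**Scale.** With SD 20 mm and 14 per arm, the standard error of an unadjusted difference is 20 × √(2/14) = 7.6 mm. A bias of 2.05 mm is 0.27 of that.

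**The case against.** The strongest reply is that subjects in pain have permitted routes. Usual care, including drug therapy, is open to both arms, and acetaminophen is supplied to all. The section 2.5.3 rule closes a paragraph on other concomitant medication and applies only when a drug is taken without notice and is also believed to matter for the assessments. Few subjects may be affected. This stands: it limits how often the rule would be used, but an off-plan analgesic or a prohibited co-treatment can still trigger removal under 2.5.3 or 2.9.

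A reader might also infer more than the documents support:

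- **That an unblinded investigator makes the decision.** Section 2.5.3 does not say who judges the drug's effect, or whether that person knows the arm.
- **That late-found ineligibility is pain-related.** It has no evident link to pain or arm. It belongs here only because it too ends data collection.
- **That the analysis becomes one of compliant survivors.** The full analysis set is meant to keep exclusions few, and only the per-protocol set is defined as free of violations. Removed subjects can remain in the full analysis set with imputed values.
- **That imputation is useless.** In the figures above it removes about a third of the bias, and more with better predictors. K-WOMAC and rescue dose are also collected at week 2. It does less for anyone removed before week 2.
- **That the analysis sets are themselves defective.** The phrase "analyzing the set of subjects excluded only for justifiable reasons" comes with no list of reasons, and neither set is named as primary, but such detail is commonly left to the SAP or full protocol. The per-protocol session counts cannot apply to controls, who have no sessions to count.

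Finally, the 20% versus 5% scenario is lopsided by construction. Section 2.3 gives 20% as an overall dropout rate, and the type I error near 17% arises only when 4 versus 0 are removed entirely according to week-4 pain.

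**Conclusion.** The point holds in a limited form. Sections 2.5.3 and 2.9 end participation without providing for further assessment, so the week-4 VAS of subjects removed before then would not be collected. Some of the reasons for removal plausibly relate to pain and, with allocation known to subjects and practitioners, may differ by arm. That relation is an inference and is not stated in the text.

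The size and direction of the bias are unknown. On the assumed inputs it is about 3 mm in completers and 2 mm after imputation at 20% versus 5% removal, about 1 mm or less at 2 versus 1 of 18, and about 0 when removal is equal. These figures depend on an SD, a correlation and removal rates that the protocol does not give. For a pilot without a power calculation, this should be fixed but is not a fatal flaw. Confidence is medium.

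**What to change.** In sections 2.5.3 and 2.9, separate stopping study treatment from stopping follow-up. When a self-taken drug, a protocol violation or late-found ineligibility comes to light, record it with its date. Continue the scheduled assessments at weeks 2, 4, 6 and 8 for every randomised subject unless consent is withdrawn. Keep these subjects in the full analysis set in their assigned arm, with the per-protocol set as supportive. The change concerns data collection only and leaves the rules on permitted treatment as they are.

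The cost is protocol wording and a few extra assessments, with no extra patients. The small downside is that the estimate will include some subjects who used off-plan treatment. The change has to be in force before the affected subjects pass week 4.
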